### Abstraction of HIVDR EWIs

Data on HIVDR EWIs will also be collected at each study phase, consisting of five variables among which EWI_1_ (*on-time pill pick-up*), EWI_2_ (*retention in care*), EWI_3_ (*pharmacy stock-outs*), EWI_4_ (*dispensing practices*), EWI_5_ (*virological suppression*). Among patients not retained in care during the 12-month follow-up period, we shall investigate to the underpinning reason that might be deliberate ART interruption, transfer out or mortality. Cases of mortality will then serve to determine the survival rate among the study participants.

#### Definition of study variables

VF will be defined as two consecutive PVL ≥ 1000 copies/ml within 1 month under intensive adherence counselling and support [10]. Participants with PVL ≥ 1000 copies/ml at any visit will therefore undergo adherence counselling and extra-visit after 1 month to confirm or infirm VF.Immunological failure will be defined as persistent CD4 < 100 cells/mm [3] during follow-up.Clinical failure will be defined as WHO clinical stage 3 or 4 events or death. Clinical management outside the study protocol will be done according to local national guidelines.HIVDR will be defined as the presence of any mutation, in the PR-RT regions of HIV-1, known to reduce the efficacy of NRTI, NNRTI or protease inhibitor, as per the *Stanford HIVdb* algorithm [18, 35, 36, 43].Good adherence will be defined as ≥95% compliance to ART (i.e. only one missing dose), measured by pill count and by self-reported, during the past 30 days.EWIs will be defined and their respective performance targets are provided below: [10, 3, 8]

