#### Eligibility criteria

##### Inclusion criteria

Will be enrolled in the study ADLHIV (aged 10–19 years), who are receiving a first- or second-line ART for ≥6 months in one of our study sites, who provide their written assent, whose legal guardian accept to provide a written informed consent (in addition to written assent provided by the adolescent), and irrespective of PMTCT antiretroviral history (exposed to PMTCT drugs, not-exposed to PMTCT drugs, or unknown exposure).

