
At enrolment, midpoint and endpoint, prevalence of VF and HIVDR (with 95% Confidence Intervals) will be described globally, by geographical settings and by site. Associated factors will be evaluated using multivariate logistic regression, with an estimative approach for the unbiased effect of ART regimens (first versus second-line) and HIV-1 diversity (CRF02_AG versus non-CRF02-AG) [18]. In order to provide the highest level of evidence amongst ADLHIV experiencing VF versus those on virological success, ART response will be described through time to event data analysis and mixed models for the trajectory of CD4 count and viral load, based on adjustments of baseline confounders (duration of treatment, age, gender, orphan hood, site). The effect of DRMs (from plasma versus buffy coat) on ART response will be evaluated using multivariate survival models, either Cox or Fine&Gray in the presence of death as competing event. Characteristics of patients LTFU will be described and, if necessary, inverse probability weights will be used. Primary outcome is the proportion of VF; secondary outcome is the proportion of acquired-HIVDR, or deaths, evaluated according to study site (referral centres versus management units), HIV-1 subtype distribution (CRF02_AG versus non-CRF02-AG) [18], adherence levels (< 95% vs. ≥95%) [44], and ART regimens (first versus second-line) [35]. Proportion of adolescents with low-level viremia (≥400 or ≥ 50copies/ml) who finally end in VF will be described, along with HIVDR profile at endpoint [45]. We will build a multivariate logistic model with predictive approach to evaluate the association of socioeconomic conditions with adherence levels and HIVDR emergence [44, 46].

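### The definition of good adherence equates ≥95% over 30 days with a single missed dose, and the two agree only at one dose a day

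*Protocol article*

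**What the plan says.** The protocol article, Definition of study variables, reads: "Good adherence will be defined as ≥95% compliance to ART (i.e. only one missing dose". The same sentence gives the measurement and the window: "measured by pill count and by self-reported, during the past 30 days". The percentage and the count are joined as restatements of one another, with no limit to any regimen or number of doses a day.

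Data collection and analysis uses the variable in two places.

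- The primary outcome (virological failure, VF) and the secondary outcomes (acquired drug resistance, HIVDR, and deaths) are evaluated by four factors: study site, HIV-1 subtype, adherence and ART line. The adherence split is given as "adherence levels (< 95% vs. ≥95" per cent. The missed-dose count is not repeated there.
- A multivariate logistic model is planned to "evaluate the association of socioeconomic conditions with adherence levels and HIVDR emergence", so adherence is also an outcome.

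Adherence is not in the adjustment set listed for the time-to-event and mixed models: "based on adjustments of baseline confounders (duration of treatment, age, gender, orphan hood, site".

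The Inclusion criteria admit adolescents "who are receiving a first- or second-line ART for ≥6 months in one of our study sites". The Background and the description of the study setting name several drug combinations, but no section says how many doses a day any of them involves.

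**The concern.** A percentage of prescribed doses and a fixed number of missed doses can be the same rule only for one particular number of prescribed doses. The definition presents them as the same rule for everyone, in a cohort that mixes first- and second-line regimens.

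The definition can therefore be followed in two ways. One site may compute a ratio and apply 95%. Another may ask how many doses were missed and call anything above one poor adherence. For a participant taking more than one dose a day, the two can give opposite answers from the same behaviour.

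The binary adherence variable is what would be affected, both as a factor for VF, HIVDR and death and as an outcome in the socioeconomic model. If dosing frequency also differed between first- and second-line regimens, the misclassification would follow ART line, which is another of the four factors compared. If the CRF held only a yes/no answer recorded under the count, the ratio could not be recovered at analysis.

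**Working it through.** **Inputs from the article.** A threshold of 95%, a count of one missed dose (read as at most one) and a window of 30 days, all from Definition of study variables.

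**Assumed input.** Doses a day, k. The article does not give it, so k = 1, 2 and 3 are shown.

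**Formula.** Prescribed doses n = 30k. With m missed, adherence = (n − m)/n. The percentage rule calls the participant good if this is at least 0.95, that is, if m ≤ 0.05n. The count rule calls the participant good if m ≤ 1.

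**Step 1: reproduce the stated equivalence (k = 1, n = 30).** 0.05 × 30 = 1.5, so the percentage rule allows at most 1 missed dose. One missed is 29/30 = 96.7% (good); two missed is 28/30 = 93.3% (not good). The two rules agree, so the article's statement is right at one dose a day.

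**Step 2: other frequencies.**

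| Doses a day | n | Most missed doses with ≥95% | Lowest adherence passing the count rule | Missed doses on which the rules disagree |
|---|---|---|---|---|
| 1 | 30 | 1 | 29/30 = 96.7% | none |
| 2 | 60 | 3 | 59/60 = 98.3% | 2 (58/60 = 96.7%) and 3 (57/60 = 95.0%) |
| 3 | 90 | 4 | 89/90 = 98.9% | 2 (97.8%), 3 (96.7%) and 4 (95.6%) |

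Every disagreement goes one way: good by the percentage, not good by the count.

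**Step 3: sensitivity to the window.** At 28 or 31 days the rules again agree only at one dose a day. At two doses a day, the percentage rule allows 2 missed of 56 (54/56 = 96.4%; 3 missed is 94.6%) or 3 missed of 62 (59/62 = 95.2%).

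**Step 4: illustrative size.** Assume two doses a day and independent misses with probability q per dose. The share on which the rules disagree is

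P(m = 2 or 3) = C(60,2) q²(1 − q)⁵⁸ + C(60,3) q³(1 − q)⁵⁷.

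| q | 1% | 2% | 3% | 4% | 5% | 7% | 8% | 10% |
|---|---|---|---|---|---|---|---|---|
| Share | 0.12 | 0.31 | 0.44 | 0.48 | 0.46 | 0.32 | 0.24 | 0.12 |

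At q = 4%, for example: 1770 × 0.0016 × 0.0937 + 34220 × 0.000064 × 0.0976 = 0.265 + 0.214 = 0.48. The maximum lies close to this value of q.

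**Step 5: from twice-daily participants to the cohort.** If a share s of participants takes two doses a day, the rest take one, and the count is applied to all, the cohort share on which the rules disagree is s times the Step 4 figure. The article does not give s. At s = 0 the result is 0%; at s = 1 it is about 12% to 48% over the q range shown. If only the percentage is applied, it is 0% whatever s is.

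**The case against.** The strongest reply is that the analysis rule is clear. Data collection and analysis gives only the percentage split, and in the definition itself the percentage comes first and the count is a gloss. If the percentage is applied, every regimen faces the same threshold and nothing is misclassified. Pill count, one of the two stated measures, naturally yields a ratio and so fits the percentage rule. The CRFs are to collect adherence data and are not shown; they may already hold the counts needed. Adherence is not in the listed adjustment set, and neither the VF definition nor the sample size depends on it.

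All of this stands, and it limits the point. It does not remove it. The analysis section does not withdraw the definition, which is where a site would look to learn what 95% means, and which offers one missed dose as the answer. Self-report is the other stated measure, and a recalled miss is naturally a count.

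A reader might infer more: that adherence will in fact be classified differently by regimen, and that the comparison of first- with second-line ART is therefore distorted. The article does not support that. It would need three things that are not stated: that some participants take more than one dose a day, that sites use the count in place of the percentage, and that dosing frequency differs between the regimens compared. If everyone took two doses a day, using the count would tighten the cut equally for all.

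**Conclusion.** The concern holds as a faulty equivalence in the definition of an analysis variable. Over 30 days, 95% and one missed dose are the same rule at one dose a day and at no higher frequency. Where the count is applied to participants taking more than one dose a day, some with at least 95% adherence would be labelled poor adherers.

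The consequence is conditional. It is 0% for once-daily participants, and 0% for everyone if the percentage cut alone is used. For twice-daily participants under the count, it is about 12% to 48% with independent misses of 1% to 10% per dose. Dosing frequency, miss rates and independence are all assumptions, so this is an illustration and not an estimate for this cohort. Misclassification that differs between regimens is possible only if dosing frequency differs between them. The sample size and the definition of virological failure are untouched.

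**What to change.** Under Definition of study variables, delete the parenthesis that equates the cut with a single missed dose, or label it as an example for one dose a day. Define adherence as doses taken divided by doses prescribed over the past 30 days, and apply the 95% cut to that ratio for every regimen. This keeps the split already stated in Data collection and analysis.

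Check that the CRF captures both doses taken and doses prescribed, and add whichever is missing.

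The cost is one sentence in the definition and, at most, a CRF field. No new visit, measurement or analysis is needed.

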### Quality assurance

For each of the 3 study phases (enrolment, midpoint, endpoint), quality assurance will be performed by proficiency testing for PVL, CD4/CD8 (cell/mm [3] and percentage) and Sanger-based GRT.

### Management of potential study risks

Lost to follow-up (LTFU) is a potential risk in reducing the power of this study for evidence-based recommendations. To limit LTFU, adherence support will be intensified and the site community relay agents will undertake active search of defaulters.

Investigators’ compliance may be concerning at certain points of the study (i.e. if a collaborator moves for several reasons). To handle this potential challenge, site visit will be conducted weekly and site compliance to study regulations will be assessed by monthly supervision. The lead applicant will regularly coordinate activities with study-site clinicians and with guidance from mentor.

Data protection and safety might be concerning. This will be handle by procurement of a new computer device and a specific database dedicated exclusively for the project, with encrypted password and a protected working station. Potential bias in laboratory data will be handled with quality assurance. To ensure functionality of equipment, routine preventive maintenance will be ensured. If for any unforeseen reason an equipment breakdown, the backup laboratory (Centre Pasteur du Cameroun) will covered the required period, under current agreement. For staff protection, biosafety will be ensured by use of personal protective equipment as per international standards, including use of for a biosafety level II cabinet for project related-laboratory activities.

### Data collection and analysis

Data will be collected per site and stored in a password-protected database at the CIRCB, Yaoundé-Cameroon, whereby the project statistician will coordinate data management and analyses using SPSS software. Study data will consist of sociodemographic, clinical and laboratory information. Data Management will be under the responsibility of the project Biostatistician of the CIRCB in Younde-Cameroon, in coordination with the principal investigator. Data management will therefore entail procedures for sociodemographic, clinical and laboratory data collection, data protection, data quality assurance and data analysis. This procedure will be similar at enrolment (M0), midpoint (M6) and endpoint (M12). Standardized Case Report Forms (CRFs) will be generated and provided to the four study sites for on-site collection of data. In addition to basic demographic information, CRFs will include all clinical information, as well as information on type of sample collected, including date, number of aliquots, volume of aliquots and sample identification numbers to reassure further tracing of laboratory results. CRFs will be translated and provided in French and in English as per national regulations in Cameroon. However, mainly the French version will be used as the study sites are all within the French-speaking sector of the country. CRFs will be completed by the project site collaborator, and double-checked by a research fellow for consistency, if necessary, the CRF will be correctly completed and signed by the site principal investigator or other authorised person. At the end of each study visit, double-checked and signed CRFs will be sent to data entry. Laboratory CRFs will be also generated and provided in paper to the corresponding local laboratories to introduce laboratory results, together with identification number of samples. At the completion of laboratory procedures, laboratory project staff will be responsible for completion of laboratory CRFs, which will be double-checked by the co-investigator for laboratory analyses and, if necessary, the CRF will be correctly completed and signed by the site principal investigator or other authorised person. At the end of this process, double-checked and signed laboratory CRFs will be sent to data entry.Data collected through clinical and laboratory CRFs will be entered on site through double entry, by designated data entry personnel. A specific database will be created for the protected entry of clinical data and laboratory results. Data storage will be done in numerical codes generated consecutively per site. Samples for plasma viral load, CD4/CD8, and eventually for genotypic resistance testing (in case of treatment failure) to be daily centralised for analysis at the CIRCB laboratory, using participant anonymous ID code for their respective sample, alongside the corresponding sample transportation form. The laboratory co-investigator at CIRCB or other authorized person will have full responsibility for the completion of any procedures.

At enrolment, midpoint and endpoint, prevalence of VF and HIVDR (with 95% Confidence Intervals) will be described globally, by geographical settings and by site. Associated factors will be evaluated using multivariate logistic regression, with an estimative approach for the unbiased effect of ART regimens (first versus second-line) and HIV-1 diversity (CRF02_AG versus non-CRF02-AG) [18]. In order to provide the highest level of evidence amongst ADLHIV experiencing VF versus those on virological success, ART response will be described through time to event data analysis and mixed models for the trajectory of CD4 count and viral load, based on adjustments of baseline confounders (duration of treatment, age, gender, orphan hood, site). The effect of DRMs (from plasma versus buffy coat) on ART response will be evaluated using multivariate survival models, either Cox or Fine&Gray in the presence of death as competing event. Characteristics of patients LTFU will be described and, if necessary, inverse probability weights will be used. Primary outcome is the proportion of VF; secondary outcome is the proportion of acquired-HIVDR, or deaths, evaluated according to study site (referral centres versus management units), HIV-1 subtype distribution (CRF02_AG versus non-CRF02-AG) [18], adherence levels (< 95% vs. ≥95%) [44], and ART regimens (first versus second-line) [35]. Proportion of adolescents with low-level viremia (≥400 or ≥ 50copies/ml) who finally end in VF will be described, along with HIVDR profile at endpoint [45]. We will build a multivariate logistic model with predictive approach to evaluate the association of socioeconomic conditions with adherence levels and HIVDR emergence [44, 46].

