With the increasing scale-up of ART, as high as 20% of children might experience virological failure (VF) in RLS, in the frame of high-levels of viremia generally observed in children. Moreover, as these children grow older, there are increasing risks of treatment failure associated to the development of HIV drug resistance (HIVDR), particularly with the limited therapeutic options available for clinical management [7, 8]. Current paediatric first-line regimens consist of lamivudine, plus abacavir or zidovudine, plus ritonavir-boosted lopinavir (LPV/r) or nevirapine (NVP), depending on the mother-child pair’s history of prevention of mother-to-child transmission (PMTCT) [6]. of note, LPV/r overcomes non-nucleoside reverse transcriptase inhibitor (NNRTI) resistance resulting from PMTCT exposure [2, 3, 9], while NVP matches with current postnatal prophylaxis [3, 8, 9]. The success of this lifelong paediatric treatment will largely depends on the effectiveness of the combination ART from childhood and monitoring overtime [8–14]. Current uptakes in PMTCT interventions and universal ART for children suggest that any infected child stands at high risk of transmitted or acquired HIVDR. Such risks are likely higher in a context whereby: (1) PMTCT practices have been varying overtime (from single dose nevirapine, AZT, to options B and B+), (2) commonly available antiretrovirals are drugs with low genetic-barrier to resistance, (3) drug stock-outs are frequently reported and (4) poor adherence remains challenging. Furthermore, these factors are associated with clinical challenges of which the high viremia in children and the limited laboratory monitoring offer room for delayed detection of treatment failure with accumulation of HIVDR mutations at rates as high as 80% [8, 10, 11, 15–21]. This situation limits therapeutic option as children grow older in SSA, thereby appealing for effective public health strategies for optimal sequencing of ART regimens, in order to maximise long-term treatment success and reduce AIDS-related morbidity and mortality in these RLS [8]. Most importantly, as older children require transitioning from pediatrics to adult ART regimens, sustaining long-term viral suppression prompts the need for reduced risks for mortality among ADLHIV in SSA [5]. With scarcity of evidence that reduces disease progression while preserving next therapeutic options for this growing population of individuals in SSA, there is need to implement an assessment that would guide efficient public health strategies in ART program performance for adolescents [2, 8].

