Within the SSA-settings, few studies have addressed the needs of ADLHIV. In South-Africa, a study comparing treatment outcomes between adolescents versus young adults at a public sector community-based ART revealed lower virological suppression rates and higher rates of VF among adolescents [31], thus underscoring the necessity for closer monitoring strategies and the eventual needs of subsequent salvage therapies [23]. In the Central African Republic, an assessment of virologic response and DRMs revealed 34% of children in need of a second-line ART after first-line failure, while 47% of those under second−/third-line ART were experiencing VF with at least one major DRM to RTIs, thus calling for urgent need for improved pediatric ART and monitoring strategies. Among Cameroonian children (aged up to 12 years), we earlier reported high rates (~ 90%) at first-line failure, after a median-time-on-ART of about two years only. Second-line guided by sequencing data showed ~ 70% with virological suppression and ~ 90% with viremia less than 1000 copies/ml. HIV-1 diversity did not interfere with emerging DRMs and CD4 showed a poor sensitivity is predicting treatment response [18]. However, data on medium- to long-term follow-up are completely missing, and recent findings showed potential implications of genetic diversity on virological response, especially among CRF02_AG infected populations [32–35], with considerable programmatic challenges as in Cameroon [36, 37]. While attempting to ascertain AIDS events among adolescents, Sharp et al. reported that, among vertically infected adolescents, the region of HIV-1-Gag targeted by CD8+ T cells as well as the magnitude of CD8+ response may have a clinical importance on monitoring disease progression [38]. With limited evidence in the management of ADLHIV in SSA, it would therefore be of great asset to thoroughly evaluate the immunovirologic response in this target population, in order to identify individual and programmatic factors to be tackled for improved quality of life and life expectancy among ADLHIV. Such analysis will help in tailoring treatment response, resistance profiling and adequacy to subsequent (second- or third-line) ART regimens for ADLHIV in need of newer therapeutic options in SSA.

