### Description of study setting

In Cameroon, a country with a generalised HIV epidemiology (4.3% prevalence in the general population) and a broadly diverse HIV strains (with the prevailing CRF02_AG recombinant) [32–36, 39], the centre region is among sites with high HIV burden (6.1%), and the locality of Yaoundé and its surrounding have a prevalence of 6.3% [40]. HIV prevalence among vertically infected children is still consistent (prevalence of 11.5%) in the country [40], and 1.2% of those aged 15–19 years are infected [39]. Altogether, these suggest a growing rate of ADLHIV in the country, with the centre region being among the most worrying. First-line ART regimens are widely used (96.3%, consisting of two nucleoside RTIs [NRTIs] plus one non-NRTI [NNRTI]) and second-line ART regimens (3.7%, consisting of one protease inhibitor and two NRTIs) are also available nationwide, with a total of 122,638 people receiving ART by end 2013 [41]. The most used regimens for adult are zidovudine plus lamivudine plus nevirapine, followed by tenofovir plus lamivudine plus efavirenz, while for children zidovudine plus lamivudine plus nevirapine and zidovudine plus lamivudine plus efavirenz are predominant [41]. In terms of ART coverage by age range, 4% of treated patients are aged 0–14 years versus 91% aged 15 and above (i.e. 5% unknown age), and adolescents (i.e. aged 10–19 years) are distributed between these two groups [41]. Importantly, the highest coverage of ART is in the centre region (Yaoundé and its surrounding), followed by the Littoral and the North-west regions [41]. The national strategic plan targets 80% ART coverage of children age 0–14 years by end 2015 [42], thus indicating a growing number of adolescents on ART.

The choice of the Centre region for the present study in Cameroon is therefore based on its high HIV burden, its high coverage of ART, the long-term experience in ART provision of health facilities [42], as well as the wide HIV-1 genetic diversity reported from vertically infected children and adolescents living in this geographical setting [18].

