#### Sample size

Assuming the rate of VF at 40%, a 95% confidence and 80% statistical power, sample size is 174 patients. Adding 10% potential LTFU during the one-year study period and 20% sequencing failure rate [10, 18], minimal sample size is 243 ADLHIV, rounded-up to 250 total sample size, further stratified into 150 ADLHIV in the referral centres (75 per site) and 100 in the HIV management units settings (50 per site), as per coverage in ART in these two geographical locations [41, 42].

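### The plan promises an unbiased effect of first- versus second-line ART from logistic regression, but the design does not support that claim and the contrast is not sized

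*Protocol article*

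**What the plan says.** All references are to the protocol article.

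- **Data collection and analysis.** At enrolment, midpoint and endpoint, the prevalence of VF and of HIVDR is described. Then "Associated factors will be evaluated using multivariate logistic regression, with an estimative approach for the unbiased effect of ART regimens (first versus second-line"), and likewise for CRF02_AG against other strains. Five baseline confounders (treatment duration, age, gender, orphanhood, site) are listed in the next sentence, which concerns the time-to-event and mixed models. VF is the primary outcome. HIVDR and death are secondary, and all are to be examined by line among other factors.
- **Sample size.** "Assuming the rate of VF at 40%, a 95% confidence and 80% statistical power, sample size is 174 patients". The allowances follow: "Adding 10% potential LTFU during the one-year study period and 20% sequencing failure rate", so that "minimal sample size is 243 ADLHIV, rounded-up to 250 total sample size". The 250 are divided by site.
- **Sampling method and Sampling strategy.** Enrolment is consecutive until each site quota is full. There is no quota or stratum by line.
- **Description of study setting.** "second-line ART regimens (3.7%, consisting of one protease inhibitor and two NRTIs) are also available nationwide". The same section gives the size of the national programme that this share describes: "with a total of 122,638 people receiving ART by end 2013".
- **Background.** Resistance is put at "accumulation of HIVDR mutations at rates as high as 80"%. For Cameroonian children up to 12 years, "we earlier reported high rates (~ 90%) at first-line failure".
- **Procedures and timeline.** Only participants with VF are genotyped. The result guides the choice among first-, second- and third-line drugs, at enrolment and again at the follow-up visits.

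**The concern.** Two separate problems meet in one sentence of the analysis plan.

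The first is bias. Line of therapy is not assigned independently of prognosis. The Background itself describes second line as what children need after first-line failure, so the second-line group is selected on earlier failure, which is closely tied to the outcome. Earlier failure is not on the list of confounders. After enrolment it gets worse: a failure found at month 0 or month 6 leads to genotyping, which can change the regimen. If line is taken as current line at months 6 and 12, the exposure is partly a consequence of the outcome.

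The second is information. The sample size rests on a single overall VF rate, and nothing secures a minimum number on second line. In the HIVDR model the outcome (any relevant mutation among failures) may be so common that few participants lack it.

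At stake is what may be concluded about line: an adjusted odds ratio described as unbiased could be both confounded and very imprecise.

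**Working it through.** **The plan's own figures.** From 174, allowing for 10% loss and 20% sequencing failure: 174 / (0.9 × 0.8) = 241.7, or 174 × 1.4 = 243.6. Both are close to the stated 243. The 174 itself cannot be rederived, because no effect size or precision is given. It corresponds to a half-width of 1.96 × √(0.4 × 0.6 / 174) = 7.3 points around 40%. Nothing in this step refers to a comparison by line.

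**Second-line count and the VF contrast.** Inputs: N = 250 and VF 40% (Sample size); second-line share 3.7% (Description of study setting). The shares of 10, 20 and 30% are assumptions.

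- Count: 250 × 0.037 = 9.25, so about 9.
- Half-width of the 95% CI for the VF difference, with 40% in both groups: 1.96 × √(0.24/n₁ + 0.24/n₂). For 241 and 9 this is 1.96 × √(0.000996 + 0.02667) = 32.6 points.
- Power: two-sided 5% test of two proportions, pooled variance under the null, 40% VF on first line against 60% on second line.

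| Second-line share | n on second line | Half-width (points) | Power, 40% v 60% |
|---|---|---|---|
| 3.7% (national) | 9 | 33 | 22% |
| 10% (assumed) | 25 | 20 | 48% |
| 20% (assumed) | 50 | 15 | 72% |
| 30% (assumed) | 75 | 13 | 83% |

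With 9 against 241, 80% power needs VF of about 84% on second line. These figures are unadjusted and before loss to follow-up.

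**The HIVDR model at one time point.** Inputs: VF 40% and sequencing failure 20% (Sample size); resistance among failures 80% and 90% (Background, the second read as a resistance rate); 70% is an assumption.

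- Sequences: 250 × 0.40 × 0.80 = 80.
- Non-resistant: 80 × 0.10 = 8; 80 × 0.20 = 16; 80 × 0.30 = 24.
- Second-line among the 80, if VF is equally common on both lines: 80 × 0.037 = 3; at assumed 10% and 20%, 8 and 16.
- If every second-line sequence is resistant, the maximum-likelihood odds ratio for line is infinite. With no effect of line, the chance of that is (resistance rate) raised to the number of second-line sequences:

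| Second-line sequences | 80% resistant | 90% resistant |
|---|---|---|
| 3 | 0.80³ = 51% | 0.90³ = 73% |
| 8 | 0.80⁸ = 17% | 0.90⁸ = 43% |
| 16 | 0.80¹⁶ = 3% | 0.90¹⁶ = 19% |

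**Bias.** No arithmetic applies. Of the two routes set out above, selection on earlier failure operates at all three visits. Regimen change after genotyping operates at months 6 and 12. Neither depends on the 3.7%.

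**The case against.** The strongest reply is that 3.7% does not describe this cohort. It is the national programme at end 2013, with 91% of patients aged 15 and above. The cohort is adolescents on ART for at least 6 months, 150 of the 250 from referral centres. The Background also cites 34% of children in a neighbouring country needing second line after first-line failure, which points to a higher share. This stands: a reader might infer that about 9 is the expected count, but the documents support it only as a low-end scenario. Hence the range of 9 to 75.

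The resistance inputs are also soft. The 80% is worded as a maximum. The sentence with about 90% does not name its quantity and concerns children up to 12. New failures at months 6 and 12 could add sequences. This too stands, and 8 to 16 is conditional on those rates.

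A reader might further infer that all the logistic models lack information. They do not: at 40% the VF model has about 100 failures and 150 non-failures, and only the second-line count limits it for this contrast. Nor can a number of events per parameter be charged to the plan, because the five listed confounders belong to the time-to-event and mixed models and the logistic covariates are not fixed.

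Finally, the choice of estimator and the handling of sparse data commonly go to an analysis plan that is not shown. That is fair, and their absence is not the finding. But the article itself states the model, the exposure and the unbiased claim, and estimator details would not make that claim true.

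**Conclusion.** The point holds in two parts of different strength.

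The claim of an unbiased effect of ART line is unsupported whatever the second-line count. Line follows from earlier failure, earlier failure is not a named confounder, and line after enrolment is partly driven by failure found in the study.

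The contrast is also unsized, and its precision is unknown because no adolescent second-line share is stated. It runs from about ±33 points (22% power for 40% against 60%) at 3.7% to about ±13 points (83% power) at an assumed 30%. Power for that 20-point difference passes 80% only towards the upper end, which nothing in the recruitment plan secures.

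For the secondary HIVDR outcome at one time point, about 8 to 16 non-resistant sequences are expected if 80 to 90% of the 80 sequences carry resistance (24 at an assumed 70%), so a non-finite odds ratio for line is a real possibility. This does not undermine the primary prevalence estimate of VF. The article's title names adolescents on both lines and does not by itself promise a comparison of lines. The change is worth making because it limits what the study may conclude about line.

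**What to change.** 1. Delete the word unbiased for ART line, and describe the result as an association.
2. Define line at enrolment for these analyses, so that regimen changes after study genotyping do not enter the exposure.
3. State the expected second-line share among adolescents at the four sites, if known. Report VF and HIVDR by line with exact CIs and the number on second line, labelled exploratory.
4. Limit the HIVDR association model to a few exposures named in advance, and fit it by penalised (Firth) likelihood.

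Resistance by drug class may be added as a less saturated outcome, but it need not replace the defined one.

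The cost is a change of analysis wording, fewer adjusted odds ratios and a weaker claim about line. Recruitment, visits and laboratory work are unaffected.
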